### Allocation to study arms

2.2.

Participants will be screened and recruited from two concussion specialty clinics, and randomization will be stratified by site. Within site, a permuted block randomization with random block sizes with a 1:1 allocation ratio will be used. The lead biostatistician will generate the randomization list which will be uploaded into the electronic data capture system. The site coordinator will receive the allocation for each participant once all eligibility information is entered and the participant is deemed eligible for the trial. Participants will be randomized to either the T-MD or usual care intervention arm. Treating clinicians and study research staff will not be blinded to participant group, as they will be employing study procedures and supervising participants in the study. The Principal Investigators will be blinded to participant group assignment throughout the study, including during data analysis.

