### Statistical analysis plan

2.6.

All data quality monitoring and analysis will be overseen by the lead biostatistician. Distributions of baseline characteristics for participants will be compared between T-MD and usual care intervention groups to assess effectiveness of the randomization. Statistical or clinical differences will be adjusted for in secondary analyses. All analyses for treatment group comparisons will use an intention-to-treat approach and results will be reported using the CONSORT extension to non-pharmacological randomized trials. The primary outcomes for this study are NSI (Aims 1, 3), PGIC scores (Aim 1) and brain activation as measured by fNIRS (Aims 2, 3). The NSI and PGIC will be measured at baseline, 2 weeks, 4 weeks, and 3 months post randomization. Brain activation will be measured at baseline and 4 weeks. NSI and fNIRS will be treated as continuous and PGIC scores will be dichotomized into minimal or no change vs. moderate or greater change. For Aim 1, we will analyze the NSI score using linear mixed models with fixed effects for site, intervention, time, and the intervention by time interaction along with a random effect for subject to control for the correlation within person over time. We will use a generalized linear mixed model with a logit link and the same fixed and random effects for the dichotomized PGIC outcome. We will test each intervention’s effect over time using the intervention*time interaction. For Aim 2, we will calculate change scores by subtracting the fNIRS value at 4 weeks from the baseline value. We will use a two-sample t-test to compare the change scores between the intervention and control group. For Aim 3, we will calculate change scores by subtracting the NSI value at 4 weeks from the baseline value. The efficacy of the intervention will be determined based on the results for each outcome and interpreted within the domain of that specific outcome with no adjustment for multiplicity. Pearson correlation will be used to examine the relationship of change in NSI to the fMRI value at 4 weeks in the intervention group.

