We also plan to explore factors (e.g., demographics, medical history, injury information, other symptoms, and impairments) that may influence the efficacy of T-MD on the outcomes of NSI, PGIC, and RTA. This will be done by focusing only on the 4-week time point and estimating within levels of each factor the intervention effect and 95% confidence intervals. We will also explore the independent effects of each treatment domain (e.g., anxiety/mood, cognitive, migraine, ocular, vestibular, sleep, autonomic) on primary and secondary clinical outcomes within the T-MD group using a mixed model with fixed effects for domain, time, and site along with a random effect for subject to control for the correlation within person over time. We will test each treatment domain’s effect over time using a domain*time interaction.

Calculations of sample size were based on the primary NSI primary outcome. We propose to randomize a total of 250 participants (125 in each intervention group) to allow approximately 200 participants for a complete case analysis at 4 weeks (assuming 20% attrition). With α = 0.05, two-tailed test, a sample size of 200 (*n* = 100 in each main effect group) will provide 80% power to detect a difference as small as 5 points on the NSI scale (standard deviation of 14) between the T-MD and usual care intervention groups assuming an autocorrelation of 0.7 for a 2 group repeated measures design with 4 repeated measures and AR (1) covariance structure. This sample size provides 99% power for the dichotomized PGIC (Aim 1) assuming 75% of the T-MD group and 50% of the control group reach moderate improvement and the same repeated measures design. Group sizes of 100 achieves 94% power to detect an effect size of 0.5 in fNIRS change using an independent samples, two-sided t-test (Aim 2, α = 0.05). For Aim 3, *n* = 100 in the intervention group provides 99% power to detect a Pearson correlation as small as 0.4. All power analyses were conducted in NCSS/PASS.

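### As written, the NSI model implies equal correlation between all visits while the sample size assumes AR(1) 0.7; if AR(1) holds and nothing else is fitted, the intervention-by-time tests are miscalibrated

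*Protocol article*

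**What the plan says.** All statements are in section 2.6 of the protocol article, Statistical analysis plan.

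- **Model.** NSI is analysed by a linear mixed model with "fixed effects for site, intervention, time, and the intervention by time interaction along with a random effect for subject". The stated purpose of the subject effect is "to control for the correlation within person over time". No residual covariance, random slope or robust standard error is named.
- **Test.** "We will test each intervention’s effect over time using the intervention*time interaction". The text does not say whether time is categorical or linear.
- **Visits.** "The NSI and PGIC will be measured at baseline, 2 weeks, 4 weeks, and 3 months post randomization". The gaps are two weeks, two weeks, and then about two months.
- **Sample size.** Power of 80% for a 5-point NSI difference (SD 14, 100 per arm, two-sided 0.05) is computed "assuming an autocorrelation of 0.7 for a 2 group repeated measures design with 4 repeated measures and AR (1) covariance structure".

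**The concern.** One random effect per subject, with independent residuals, gives the same correlation for baseline with 2 weeks as for baseline with 3 months. AR(1) at 0.7 gives 0.70, 0.49 and 0.34 at one, two and three visits apart. So the model as written cannot represent the covariance on which the trial was sized.

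This matters because the named test is the intervention-by-time interaction. Its standard error depends directly on the within-person covariance, so a wrong structure feeds straight into the p-value. NSI is also the outcome on which the sample size rests. The uneven visit spacing makes one common correlation less plausible still.

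**Working it through.** **Inputs from section 2.6.** SD 14; 100 per arm; four visits; AR(1) 0.7; two-sided alpha 0.05. Section 2.2 gives 1:1 allocation. Complete data are assumed throughout.

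**1. The plan's own figure.** Take group differences of 0, 5, 5, 5 over the four visits, categorical time and AR(1) 0.7. The 3-df interaction test then has noncentrality 11.06 and power 80.6% (chi-square), or 79.8–80.3% (F). The stated 80% is reproduced on this reading. The article does not say which test was powered; a comparison of four-visit means under AR(1), for instance, gives 86.6%.

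**2. What the random-subject model estimates under AR(1).** With complete data it pools to the mean pairwise correlation:

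(3 × 0.70 + 2 × 0.49 + 0.343) / 6 = 0.5705.

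Its standard error for any baseline-to-visit group contrast is

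14 × √[2(1 − 0.5705) × 2/100] = 1.84.

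**3. The correct standard error.** It is 14 × √[2(1 − ρ) × 2/100], with ρ the true correlation of that visit with baseline. The actual type I error is 2[1 − Φ(1.96 × model SE / true SE)].

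| Contrast from baseline | ρ | True SE | Model SE / true SE | Type I error |
|---|---|---|---|---|
| 2 weeks | 0.70 | 1.53 | 1.20 | 1.9% |
| 4 weeks | 0.49 | 2.00 | 0.92 | 7.2% |
| 3 months | 0.343 | 2.27 | 0.81 | 11.3% |

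A simulation of 20,000 null trials gives 2.1%, 7.3% and 11.6%.

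**4. Decay by calendar time instead of visit order.** Assume 0.7 per 2 weeks and 3 months = week 13; neither is stated in the article. Correlations with baseline are then 0.70, 0.49 and 0.7^6.5 = 0.098. The mean pairwise correlation is 0.388 and the model SE is 2.19.

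| Contrast from baseline | True SE | Model SE / true SE | Type I error |
|---|---|---|---|
| 2 weeks | 1.53 | 1.43 | 0.5% |
| 4 weeks | 2.00 | 1.10 | 3.2% |
| 3 months | 2.66 | 0.82 | 10.6% |

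**5. The named test, time categorical (3 df).** Under AR(1) the model's statistic is a weighted sum of three 1-df chi-squares. The weights are 0.47, 0.77 and 1.76 by visit order (sphericity epsilon 0.77). Type I error is 6.3% by visit order (6.4% simulated) and 6.5% by calendar time.

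**6. The named test, time linear (1 df).** Let c be the centred time scores, R the true correlation matrix and ρ̄ its mean pairwise correlation. Type I error is 2[1 − Φ(1.96 × √{(1 − ρ̄)c′c / c′Rc})]. With visit-number scores and AR(1) by visit order, c′c = 5 and c′Rc = 3.7365. The variance ratio is 3.7365 / (0.4295 × 5) = 1.74, which gives 13.7%. The other combinations give:

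- week scores, AR(1) by visit order: 11.5%
- visit-number scores, calendar decay: 11.0%
- week scores, calendar decay: 14.1%

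**7. Controls.** With true equal correlation of 0.57, the random-subject model gives 4.9–5.2% throughout. With an unstructured covariance and AR(1) 0.7 true, 10,000 null trials give 4.9%, 4.5% and 4.9% by visit and 4.7% jointly.

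**The case against.** The strongest reply is that the article neither calls the subject effect an intercept nor says that it stands alone. A mixed model can carry a subject effect beside an AR(1) or unstructured residual. A full analysis plan, not shown here, may specify that, and the sample-size paragraph does name AR(1) for this same design. This stands as a limit on the claim: a reader might infer that a bare random intercept is certain to be fitted, and the text does not establish it. It does not remove the mismatch, because the article states one device for within-person correlation and sizes the trial on a structure which that device alone cannot produce.

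Three further stronger readings are tempting and also fail.

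- **That the NSI standard errors are simply wrong.** AR(1) 0.7 is a planning input, not a known property of NSI data. Under equal correlation the stated model is sound.
- **That 4-week intervals are too narrow.** They are if correlation decays by visit order (7.2%), but slightly too wide if it decays by calendar time (3.2%).
- **That the primary test runs at 11%.** The 3-month contrast is not designated as a test. With categorical time the named interaction is only mildly inflated; it reaches 11–14% only if time is linear, which the article leaves open.

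**Conclusion.** The point holds as a conditional inconsistency between two stated choices. If AR(1) 0.7 is true and the random subject effect is all that is fitted, the interaction test exceeds its nominal 5%: by little with categorical time, and to more than double with a linear trend. The 3-month contrast is anti-conservative at about 11%, the 2-week contrast is conservative, and the 4-week contrast can go either way.

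The results assume complete data, 100 per arm and a constant SD of 14. The calendar-time figures also rest on 0.7 per 2 weeks and week 13. The stated 80% power is not shown to be wrong. If the sponsor does not believe AR(1), the tests may be well calibrated, but the power calculation then rests on a different covariance from the analysis. Either way the two statements need reconciling.

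**What to change.** Fit NSI with an unstructured within-subject covariance over the four visits: four variances and six covariances, 10 parameters, which 200–250 participants support. Use Kenward-Roger degrees of freedom. Name as fallback the random subject effect with robust standard errors. If the full analysis plan already specifies a residual covariance, it is enough to confirm that it allows correlation to fall with time and to describe the model that way.

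The sample size is unchanged. The cost is a few more covariance parameters and one line of text and code, best settled before outcomes are analysed.

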**Methods:**

This study employs a single-blinded, two-group repeated measures design. The RCT will enroll up to 250 military-aged civilians (18-49 yrs) with a diagnosed complex mTBI within 8 days to 6 months of injury from two concussion specialty clinics. The two study arms are a T-MD intervention and a usual care, behavioral management control group. All participants will complete a comprehensive, multidomain clinical evaluation at their first clinical visit. Information gathered from this evaluation will be used to adjudicate mTBI clinical profiles. Participants will then be randomized to either the 4-week T-MD or control arm. The T-MD group will receive targeted interventions that correspond to the patient’s clinical profile (s) and the control group will receive behavioral management strategies. Primary outcomes for this study are changes from enrollment to post-intervention on the Neurobehavioral Symptom Inventory (NSI), Patient Global Impression of Change (PGIC), and functional near-infrared spectroscopy (fNIRS). Time to return to activity (RTA), and healthcare utilization costs will also be assessed.

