The overall objective of this multisite RCT is to determine the effectiveness of a T-MD intervention compared to usual care (behavioral management) in military-aged civilians with complex mTBI (anxiety/mood, cognitive, migraine, ocular, vestibular, sleep, and autonomic domains). The study involves three primary aims: (1) compare using an RCT the effectiveness of T-MD (anxiety/mood, cognitive, migraine, ocular, vestibular, sleep, autonomic domains) intervention to usual care (behavioral management) on improving clinical profile-based outcomes including symptoms, impairments, return to activity (RTA), and healthcare utilization costs in 200 military-aged civilian patients with complex mTBI; (2) to compare changes in brain activation (i.e., CBF) as measured by fNIRS in the T-MD and usual care intervention groups; and (3) to correlate changes in symptoms and impairment with brain activation as measured by fNIRS. We will also explore factors (e.g., demographics, medical history, injury information) that may influence the efficacy of T-MD on NSI, PGIC, and RTA outcomes.

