#### Primary and secondary study outcomes

2.4.3.

Primary outcomes are the Neurobehavioral Symptom Inventory (NSI), Patient Global Impression of Change (PGIC), and Functional Near-infrared Spectroscopy (fNIRS). These primary outcomes represent different domains of function that are commonly affected following mTBI and provide different sources of information about the injury that inform clinical care decisions (i.e., treatment and/or rehabilitation). The NSI gathers specific information about mTBI symptoms. This measure is comprised of 22 items scored from 0 to 4 (0 total score represents no mTBI-related symptoms, 88 total score represents very severe levels of all 22 mTBI-related symptoms). The PGIC captures patient self-reported assessment of changes in their overall quality of life throughout their mTBI recovery. The prompt for the PGIC is: “Since beginning treatment at this facility, how would you describe the change (if any) in activity limitations, symptoms, emotions and overall quality of life related to your post-concussive condition?” The patient responds on a scale ranging from 0 (No change or condition has gotten worse), to 7 (A great deal better and a considerable improvement that has made all the difference). The fNIRS is a non-invasive imaging tool that measures changes in cerebral blood flow (CBF) and oxygenation in response to a behavioral task. The current study utilizes three neurocognitive tasks (WAIS symbol search and coding, and a flanker task) and a resting condition. Brain activation and deactivation in brain regions of interest (ROIs) will be examined and compared between groups within the first week following enrollment and at approximately four-weeks after enrollment. Secondary outcomes will include data from symptom, neurocognitive, balance, vestibular, sleep, and physical activity assessments (see Table 2). In addition, participant demographics and medical history data will be gathered as part of the normal clinical interview for mTBI (e.g., age, sex, history of mTBI, migraine). A daily text message-based assessment will be used to evaluate each participant’s compliance with their assigned intervention; and to assess frequency and intensity of at-home exercises in between the initial, 2-, and 4-week in-person study intervals. A FitBit Inspire 2 activity monitor will be provided to each participant to track activity and sleep throughout the 4-week intervention period. A detailed description of all study measures, scoring, and validity is presented in Supplemental material (see Description of Measures).

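### The primary fNIRS comparison (Aim 2) is an unadjusted t-test on change scores that leaves out baseline fNIRS and site; the subtraction order also needs a label

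*Protocol article*

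**What the plan says.** All of this is in the Protocol article.

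- **Derivation and test (2.6, Statistical analysis plan).** fNIRS is listed there among the primary outcomes, for Aims 2 and 3. On timing: "Brain activation will be measured at baseline and 4 weeks". For Aim 2, "we will calculate change scores by subtracting the fNIRS value at 4 weeks from the baseline value", and then "We will use a two-sample t-test to compare the change scores between the intervention and control group". No covariate is named for this comparison.
- **The Aim 1 models, same section.** The mixed models for NSI and dichotomized PGIC carry a fixed effect for site.
- **Allocation (2.2).** Randomization is stratified by site.
- **Baseline differences (2.6).** Differences found between the arms at baseline are to be adjusted for in secondary analyses.
- **Power (2.6).** With 100 per group, the plan states 94% power for an effect size of 0.5 in fNIRS change, by a two-sided t-test at α = 0.05.
- **Direction of change.** The abstract says "Primary outcomes for this study are changes from enrollment to post-intervention on the Neurobehavioral Symptom Inventory (NSI"), and continues with PGIC and fNIRS. For Aim 3 the section repeats the Aim 2 subtraction: "we will calculate change scores by subtracting the NSI value at 4 weeks from the baseline value". The Introduction words Aim 2 as "to compare changes in brain activation (i.e., CBF) as measured by fNIRS in the T-MD and usual care intervention groups". Section 2.4.3 says "Brain activation and deactivation in brain regions of interest (ROIs) will be examined and compared between groups".

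**The concern.** The plan collects a baseline fNIRS value from each participant but uses it only by subtraction. Subtraction fixes the slope of the 4-week value on baseline at 1. When the two visits have the same variance the true slope is r, the correlation between them, which is below 1. The t-test therefore carries avoidable noise from baseline into the comparison. It also omits the one factor that the design stratifies on, while the Aim 1 models include it. At stake is the precision of one of three primary outcomes, for which the data needed are already in hand.

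A smaller point concerns the sign. As written, change is baseline minus 4 weeks, so a rise in activation is tabulated as a negative change. That is opposite to how change from enrollment to post-intervention is usually read. The protocol examines both activation and deactivation, so a reader could not detect an unexpected sign from clinical sense.

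**Working it through.** **Inputs from 2.6:** 100 per group; effect size 0.5 in SD units of the change score; two-sided α = 0.05; stated power 94%.

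**Assumed, not in the document:** equal fNIRS variance (set to 1) at baseline and 4 weeks; baseline-to-4-week correlation r between 0.3 and 0.7. The middle value, 0.49, is 0.7², which borrows the plan's AR(1) value of 0.7 for NSI at lag 2 (baseline, 2 weeks, 4 weeks). It is not an fNIRS figure.

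**1. Reproduce the plan's figure.** Noncentrality = 0.5 × √(100/2) = 3.536, with 198 degrees of freedom. Power from the noncentral t distribution is 94.0%, and the normal approximation gives 94.2%. The stated 94% is reproduced.

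**2. Variance under each analysis.** Per participant:

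- change score: 2(1 − r)
- 4-week value adjusted for baseline: 1 − r²
- ratio: (1 − r²) / [2(1 − r)] = (1 + r)/2

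**3. Power with the same raw treatment effect.** The effect size becomes 0.5/√((1 + r)/2), and noncentrality is that value × √50.

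| r | Change variance | Adjusted variance | Ratio | Variance cut | Effect size | Power |
|---|---|---|---|---|---|---|
| 0.3 | 1.40 | 0.91 | 0.65 | 35% | 0.620 | 99.2% |
| 0.49 | 1.02 | 0.76 | 0.745 | about 25% | 0.579 | 98.3% |
| 0.7 | 0.60 | 0.51 | 0.85 | 15% | 0.542 | 96.8% |

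Put as sample size, at r = 0.49 the adjusted analysis would match the t-test on 200 completers with about 200 × 0.745 = 149. No gain is counted for site, because the document gives no between-site variance for fNIRS.

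**4. Subtraction order.** Baseline minus 4 weeks equals −(4 weeks minus baseline). One simulated trial (100 per arm, assumed true rise of 0.5 under T-MD) gives:

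| Rule | T-MD minus usual care | 95% CI | t | p |
|---|---|---|---|---|
| Baseline minus 4 weeks, as written | −0.446 | −0.708 to −0.185 | −3.36 | 0.00093 |
| 4 weeks minus baseline | +0.446 | 0.185 to 0.708 | 3.36 | 0.00093 |

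Power is 94.0% for an effect of +0.5 and for −0.5. Only the sign changes.

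**The case against.** A t-test on change scores is valid and unbiased under randomization, and adjustment is a choice about efficiency. The test already has 94% power, the gain rests on a correlation that the document does not give, and baseline differences are to be handled in secondary analyses.

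Validity is granted, and so is the uncertainty in r: the gain shrinks as r approaches 1. But under equal variances the ratio (1 + r)/2 is below 1 for every r below 1, so the direction of the gain does not depend on the assumed value. Secondary adjustment for observed imbalance does not improve the precision of the primary estimate. The 94% also holds only if the effect is as large as assumed; for a smaller effect, precision matters more.

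On the sign, a reader might infer that the planned score reverses the endpoint that the protocol defines, and so makes the fNIRS result wrong. The document does not support that. The abstract names two time points and gives no formula or sign. The only explicit formula is the one in 2.6, and it is used for both fNIRS and NSI. No direction of fNIRS response is called better, so a negative score is not declared to be worsening. A reader might also infer that NSI carries opposite signs in Aims 1 and 3. But Aim 1 derives no change score, and the sign of its interaction contrast depends on coding that the article does not give. Baseline minus 4 weeks is a legitimate convention, and for NSI it makes improvement positive. What stands is that the score is not labelled as a decrease.

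**Conclusion.** The point holds as one of efficiency and consistency. The primary Aim 2 analysis discards usable baseline information and omits the stratification factor that the Aim 1 models include. Under equal variances and r of 0.3 to 0.7, adjusting for baseline cuts the variance of the comparison by 35% to 15% and raises power from 94% to about 97–99%. The benefit of adding site is unquantified. The planned t-test remains valid.

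The subtraction order is a minor labelling matter. It affects the sign of reported estimates and confidence limits. The two-sided p-value, standard error, interval width and power stay the same. In Aim 3, where change in NSI is correlated with a 4-week imaging value, the sign of the correlation likewise follows the NSI subtraction order and its strength does not.

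**What to change.** In 2.6, replace the Aim 2 t-test with a linear model of the 4-week fNIRS value on intervention, baseline fNIRS and site. Report the intervention effect as T-MD minus usual care with its 95% confidence interval. The t-test on change can stay as a supporting analysis.

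Wherever change scores are kept, for fNIRS or for NSI in Aim 3, either define change as 4 weeks minus baseline, or keep the present formula and label the result as a decrease from baseline.

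The cost is a few sentences in the analysis plan, settled before the data are analysed. No extra participants, visits or measurements are needed, and the sample size can stay as it is.

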Previous research on the effectiveness of treatments for mTBI has been limited in that only single treatments [e.g., (16)] have been used and/or multiple treatments have been applied across all patients groups without regard to specific symptoms and impairment or clinical profiles. In addition, when multiple treatments have been applied, separate treatment effects for each intervention were not considered [e.g., (17)]. The T-MD intervention in the current proposal will implement targeted interventions for seven affected domains including: (1) anxiety/mood, (2) cognitive, (3) migraine, (4) ocular, (5) vestibular, (6) sleep, and (7) autonomic. Each intervention will target a specific affected domain (e.g., vestibular rehabilitation for a patient with vestibular impairment and/or symptoms), but not all patients will receive all interventions. This approach better reflects precision clinical care models and may provide a more effective and efficient therapeutic pathway for patients with complex mTBI.

Research on the effectiveness of treatment following mTBI has yet to provide concomitant evidence of changes in the brain that may underly clinical findings. Functional near-infrared spectroscopy (fNIRS) is an optical imaging technique that measures temporal–spatial changes in oxygenated (activation) and deoxygenated (deactivation) hemoglobin concentrations in the cerebral cortex and is highly correlated with cerebral blood flow (CBF). Functional NIRS provides an objective measure of brain injury *via* changes in CBF that correspond to functional impairments in cognition (18) and vestibular function (19). Functional NIRS may provide an objective measure of treatment effectiveness by evaluating changes in brain activation at rest and during a cognitive paradigm in conjunction with clinical outcomes.

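### Aim 3 pairs change in NSI with a single 4-week brain value, mislabelled fMRI, where the outcome definition and rationale point to change in fNIRS

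*Protocol article*

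**What the plan says.** The analysis for Aim 3 is fixed in the Protocol article, section 2.6 (Statistical analysis plan): "Pearson correlation will be used to examine the relationship of change in NSI to the fMRI value at 4 weeks in the intervention group". The change score prepared for it is for the NSI only: "For Aim 3, we will calculate change scores by subtracting the NSI value at 4 weeks from the baseline value".

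The same section names fNIRS as the brain measure for Aims 2 and 3, and gives its timing: "Brain activation will be measured at baseline and 4 weeks". A change score for fNIRS exists, but is assigned to the other aim: "For Aim 2, we will calculate change scores by subtracting the fNIRS value at 4 weeks from the baseline value".

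The Introduction words Aim 3 as "to correlate changes in symptoms and impairment with brain activation as measured by fNIRS", with no restriction to one arm. Earlier in the Introduction the case for the instrument is that "Functional NIRS may provide an objective measure of treatment effectiveness by evaluating changes in brain activation at rest and during a cognitive paradigm", read together with clinical outcomes. The Methods paragraph of the abstract lists the primary outcomes, fNIRS among them, as changes from enrolment to post-intervention.

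The power paragraph of section 2.6 gives 99% power to detect a Pearson correlation as small as 0.4 with n = 100 in the intervention group. It does not say whether that correlation involves a brain level or a brain change.

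**The concern.** Two things in the operative sentence do not fit the rest of the protocol.

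First, the instrument. fNIRS is the brain measure in the abstract, the aims, the outcome section, Table 2, the Figure 1 legend and the power paragraph. fMRI appears only in this sentence.

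Second, and more important, the quantity. Symptoms enter as a change and the brain measure enters as a single follow-up value. That value carries whatever distinguished participants before treatment as well as anything that changed during it. In a comparison between randomised arms a follow-up value can serve, because randomisation balances the baseline on average. A correlation inside one arm has no such protection.

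Aim 3 is one of three aims that the Introduction calls primary, and the Discussion offers imaging that corroborates the clinical findings as a deliverable. As written, the result could be read as evidence that symptoms and brain function recover together when the analysis does not address that question.

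**Working it through.** **1. The plan's own power figure.** Inputs from the power paragraph of section 2.6: n = 100 (T-MD arm), r = 0.4. A two-sided alpha of 0.05 is stated for the NSI calculation and assumed here for Aim 3. By Fisher's z:

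- power = Φ(atanh(r) × √(n − 3) − 1.960)
- atanh(0.4) = 0.4236 and √97 = 9.849, with product 4.172
- power = Φ(4.172 − 1.960) = Φ(2.212) = 98.7%

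A simulation of the t-test for r (200,000 runs) also gives 98.7%. The stated 99% is reproduced.

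**2. What the level correlation contains.** Write D for NSI change, F0 and F4 for fNIRS at baseline and 4 weeks, and C = F0 − F4 for fNIRS change, in the direction that the protocol uses. Then F4 = F0 − C, and

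- cov(D, F4) = cov(D, F0) − cov(D, C)

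The quantity of interest is cov(D, C). The planned analysis mixes it with cov(D, F0), the relation of symptom recovery to where the participant's brain measure started. Two consequences follow without further assumptions:

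- If symptom change is unrelated to brain change, cov(D, C) = 0 but cov(D, F4) = cov(D, F0). The level correlation is non-zero whenever baseline activation goes with recovery.
- If cov(D, F0) = cov(D, C), both non-zero, the level correlation is zero although the changes are linked.

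**3. The repaired analysis.**

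- *Change with change, T-MD arm.* The power formula depends only on r and n, so r = 0.4 at n = 100 again gives 98.7%.
- *4-week fNIRS adjusted for baseline fNIRS.* Given F0, C is a linear function of F4, so the partial correlation with D has the same size for either. One covariate replaces n − 3 by n − 4: Φ(0.4236 × √96 − 1.960) = Φ(4.151 − 1.960) = Φ(2.191) = 98.6%, for a partial correlation of 0.4.
- *Both arms, if added.* At n = 200 and r = 0.4: Φ(0.4236 × √197 − 1.960) = Φ(5.946 − 1.960) = Φ(3.986), above 99.9%.

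**The case against.** The best defence is the wording of Aim 3. In "to correlate changes in symptoms and impairment with brain activation as measured by fNIRS", the word for change attaches to symptoms and impairment, while Aim 2 in the same sentence speaks of changes in brain activation. The Discussion likewise speaks of correlating outcomes with brain function. A level analysis is compatible with that wording. This stands: the plan does not flatly contradict its aim. It does not remove the mismatch with the abstract, which defines the fNIRS outcome as change, or with the rationale of fNIRS as evidence "by evaluating changes in brain activation at rest and during a cognitive paradigm in conjunction with clinical outcomes".

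The wrong instrument name would mislead no analyst, since the same section names fNIRS for Aims 2 and 3. That also stands; it is a one-word correction.

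A reader might infer that the planned analysis is underpowered. The document does not support this. It never says that the 0.4 is a change-with-change correlation, and any translation to a level needs the correlation s between fNIRS at baseline and 4 weeks, which is not given, together with further assumptions. Suppose the change-with-change correlation is 0.4 and the variances at the two visits are equal:

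- If NSI change is unrelated to baseline fNIRS, the level correlation is 0.4 × √(2(1 − s)) in size. At s = 0.5 that is 0.40, with power 99%; below s = 0.5 there is no loss.
- If the 4-week level relates to NSI change only through fNIRS change, it is 0.4 × √((1 − s)/2). At s = 0.5 that is 0.20, with power 51%.

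Two admissible assumptions disagree this widely, so a power loss should not be stated as a finding.

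A reader might also infer that using one arm prevents Aim 3 from being answered. It does not. The restriction appears consistently in the analysis and the power paragraph, and an association between changes can be shown within T-MD. What one arm cannot show is whether the association differs from that under usual care, a question that Aim 3 does not expressly pose.

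**Conclusion.** The point holds in a limited form. The Aim 3 sentence names an instrument that the trial does not use, and it pairs a symptom change with a 4-week brain level although the baseline measurement is available, its change is already derived for Aim 2, and the abstract and Introduction present the fNIRS outcome and purpose as change. As written, the correlation does not estimate whether symptom change tracks brain change. That conclusion rests on the algebra above and on no assumed value.

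The size of the distortion cannot be given, because the document reports neither the relation of baseline fNIRS to symptom change nor the stability of fNIRS over 4 weeks. The 99% power is correct for the correlation and sample size stated. The randomised comparisons for NSI, PGIC and fNIRS are unaffected.

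**What to change.** In section 2.6, replace the brain variable in the Aim 3 sentence. Suggested wording: *For Aim 3, change in NSI from baseline to 4 weeks will be related to change in fNIRS over the same interval by Pearson correlation in the T-MD arm.* An acceptable alternative keeps the 4-week fNIRS value and adjusts it for baseline fNIRS. In the power paragraph, state which correlation the 0.4 refers to. Since both change scores are baseline minus 4 weeks, say in words what a positive correlation means.

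As an optional addition, report the same association in the usual care arm, or in both arms with a term for arm, so that the T-MD result can be set beside recovery under usual care. No power is claimed for an interaction between arm and change.

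The cost is a change of wording and, for the addition, a little more analysis. All measurements are already scheduled and no further participants are needed. The choice should be made before the data are analysed, because choosing between level and change afterwards would be post hoc.
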